##### Work ability

Work ability will be measured as improved working ability and reduction in work-related stress. The measure is self-reported work ability assessed by three items from the Work Ability Index. The items concern perceived work ability in relation to physical and mental demands at work and the employee’s prognosis of his/her work ability two years hence [34].

##### Sickness presenteeism and work performance

Sickness presenteeism will be measured by the single question: ‘Did you, in the last six months, go to work even though you felt that you really should have taken sick leave because of your state of health?’ [35]. The response format is a 4-point scale ranging from 0 (never) to 4 (more than 5 times). This item has been extensively used in previous research [35, 36]. In addition, two items about impairment of work performance due to 1) health problems (presenteeism) and 2) work-environment problems will be assessed. The first has been developed and adapted from the Work Productivity Impairment – General Health Questionnaire [37]; the second has been developed and tested for validity and reliability in Sweden [38]. The response format for both is 0 to 10, with higher scores indicating that health problems or work-environment problems have prevented the employee from working.

##### Health problems

HRQoL will be assessed by the EuroQoL health state questionnaire (EQ-5D). The response format is a 3-level scale, with higher levels indicating severity [39]. We will use the subscale for insomnia from the Karolinska Sleep Questionnaire, to assess sleeping problems. The response format range from 0 (never) to 5 (always), higher scores indicate severity [40].

##### Prognostic measures

A variety of prognostic measures for sick leave will be included in the study. At baseline, participants’ personal characteristics (e.g. age, gender, marital status, educational level), workplace characteristics (e.g. sector, profession) and sick leave two years before inclusion will be collected from the LISA and MiDAS registers. In addition, questions covering all dimensions from the demand-control-support model [41] will be included as a prognostic variable. Psychological and social factors at work and work-family balance will be assessed by items from the General Nordic Questionnaire [42] which focus on ongoing conflicts with the employer/superior, perceived loss of control over work tasks, conflicts between the employee’s values and how work is carried out and work-family balance. Organizational factors at work will be assessed by items from the Copenhagen Psychosocial Questionnaire [43] with focus on the emotional demands made by the employee’s work. Finally, the employee’s self-efficacy in RTW will be assessed as a prognostic factor [44].

Information about treatment (i.e. psychological counseling, number of sessions, use of antidepressants) and health care consumption will be collected from employees’ medical records and the Vega register from baseline until the 18-month follow-up.

### Process evaluation

As recommended by Moore GF*,* et al. [45], a process evaluation will be conducted. The process evaluation [46] will examine (1) the study’s fidelity, i.e. whether and to what extent it is possible to implement the intervention according to the protocol, (2) reach, dose delivered and dose received, i.e. the relationship between the key elements of the intervention and the effect outcome, and (3) the study’s context, i.e. how the RCs, the persons on sick leave, their employers, their physicians and other stakeholders (e.g. occupational health service, social insurance agency officer) perceive the intervention and the obstacles and enablers which influence the implementation. Process-evaluation data will be collected by means of questionnaires, employees’ medical records and individual interviews with RCs, employees and their employers.

*Fidelity* will be measured by a questionnaire containing questions about whether the intervention was delivered as planned. The RCs in the intervention group will report overall adherence to the manual/fidelity to the method for each employee during the study, after the employee has participated in the problem-solving process. *Reach* is measured for RCs and employees. The RCs participation in the two-day training course will be assessed by attendance and their satisfaction with the course. Eligibility will be screened by medical records, while reach will be assessed as those who are willing to participate in the study. *Dose delivered* will be assessed by means of a questionnaire for the RCs which asks questions about the frequency of face-to-face meetings with the employee, number of telephone follow-ups and the frequency and quality of the three-party meetings with the employer. *Dose received* is defined as the whether or not the participants receive the problem-solving intervention. Dose received will be measured by how much of the intervention that the participants received; number of sessions with the RC; how much the participants were exposed to the different components of the intervention. The content and fulfillment of the recommended follow-ups with the employees will be addressed. The RCs in the control group will receive a check list which helps them to report the content in the control condition.

### Economic evaluation

A cost-utility analysis will be conducted to analyze changes in HRQoL measured by EQ-5D and translated using the Swedish experience-based value set [39] and societal costs. Direct costs for health care will be estimated based on administrative data from the Vega register. Indirect costs will be estimated using the human capital approach from sick leave (self-reported and registered in MiDAS) and self-reported presenteeism. All-cause health care use will be collected from the Vega register over 18 months after baseline. This register covers diagnoses, the reason for visits and measures taken for patients visiting primary and specialized healthcare in the Västra Götaland region of Sweden [47].

Moreover, a cost-effectiveness analysis will be conducted to compare changes in days on sick leave to the direct health care costs, including the costs for conducting the intervention, calculated based on time reported by the RCs.

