### Recruitment of rehabilitation coordinators

RCs were recruited from PCCs in the Västra Götaland region. Information about the study was sent to managers in the region by the first author ([name]) and was given at meetings with PCC managers and RCs. Only RCs not participating in other ongoing interventional studies at the time of inclusion were invited to participate. RCs were also excluded if they had an upcoming leave of absence (for example pregnancy leave, a sabbatical) or if they were leaving the PCC or retiring. About 80 coordinators received an invitation. Written information about the study was provided as well as a registration form and informed consent. Written informed consent was obtained from all RCs. The recruitment process resulted in 19 RCs covering 24 PCCs.

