### Primary outcome

#### Registered sick leave

The primary outcome is the total number of days of sick leave 18 months after baseline. Data from MiDAS will be collected from baseline until the 18-month follow-up and for the 24 months before baseline. Information about the number of days on sick leave, episodes of sick leave after RTW, and receipt of disability pension will be collected for all participants. Sickness benefit and disability pension will be analyzed separately.

The total number of days of registered sick leave will be calculated after 36 months in the same way as at the 18-month follow-up.

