##### Statistical power

We estimate that the study population needs to be 220 participants: 110 participants in the intervention and the control group respectively. The participants will be obtained by sampling 10 clusters with 11 participants each in the intervention group and the same number of clusters and participants in the control group. With these numbers it will be possible to achieve around 80% power to detect a difference between the groups of at least 20% of registered sickness absence 18 months after baseline. The intra-cluster correlation was set to 0.010. This sample size calculation is relevant for statistical analyses that take into account a correction factor for the effect of a clustered design and use an alpha level of 0.05.

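### Health care use is extracted only from baseline onward, so direct health care cost cannot be adjusted for each participant's own prior cost

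*Protocol article*

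**What the plan says.** The protocol article gives the health care window twice. Under Economic evaluation: "All-cause health care use will be collected from the Vega register over 18 months after baseline". Under Prognostic measures: "health care consumption will be collected from employees’ medical records and the Vega register from baseline until the 18-month follow-up". No section collects health care use from before baseline.

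The window for registered sick leave is different. Under Registered sick leave: "Data from MiDAS will be collected from baseline until the 18-month follow-up and for the 24 months before baseline". The Prognostic measures section also lists sick leave in the two years before inclusion as a baseline characteristic.

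On the source of costs, Economic evaluation says: "Direct costs for health care will be estimated based on administrative data from the Vega register". It adds: "Indirect costs will be estimated using the human capital approach from sick leave (self-reported and registered in MiDAS) and self-reported presenteeism". The cost-utility analysis uses societal costs. The cost-effectiveness analysis sets days of sick leave against direct health care costs, with the cost of delivering the intervention included.

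The coordinator is the unit of randomisation, stratified by the care-need index of the health care centres. On the number of clusters: "The recruitment process resulted in 19 RCs covering 24 PCCs". The Data analysis section allows adjustment for potential confounders that turn out to be unevenly distributed.

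**The concern.** What a person consumed in health care before entry is the natural predictor of what that person consumes afterwards, particularly when all-cause use in primary and specialised care is counted. The plan recognises this logic for sick leave, where it takes a two-year history, but not for health care, although that too comes from a register that can be queried backward.

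Starting points may well differ between participants. They join with a current sick leave spell of 2 to 12 weeks, so the care already used in that spell varies and lies outside the extraction window. The care-need index describes the population of a centre (age, education, employment, household) and not a participant's own use of care.

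The adjustment rule in Data analysis does not help. An imbalance in prior health care use can be neither seen nor corrected directly if the data are never requested. This is a data window fixed in the article. A later analysis plan can choose covariates, but only among data that were extracted.

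At stake is the precision of the incremental direct cost, and how far that estimate depends on the luck of the allocation. The primary outcome is not affected.

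**Working it through.** **No figure to reproduce.** The article gives no precision or power figure for costs. Its power statement concerns registered sick leave and does not bear on this point.

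**Inputs from the article.** 220 participants; intra-cluster correlation (ICC) 0.010, set for sick leave; 19 coordinators recruited. The design assumed "sampling 10 clusters with 11 participants each in the intervention group and the same number of clusters and participants in the control group".

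**Assumptions.** 19 coordinators split 10 and 9, with equal cluster size m = 220/19 = 11.58. ICC for cost of 0.01, 0.05 or 0.10. Correlation r between prior and later health care cost of 0.3, 0.5 or 0.7. The article gives neither a cost ICC nor r. The formulas below are for a linear model on the cost scale.

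**Step 1: gain from adjustment.** The individual-level variance is multiplied by 1 − r² and the confidence interval width by √(1 − r²).

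| r | 1 − r² | √(1 − r²) |
|---|---|---|
| 0.3 | 0.91 | 0.95 |
| 0.5 | 0.75 | 0.87 |
| 0.7 | 0.51 | 0.71 |

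**Step 2: the gain if prior cost explains nothing between coordinators.** The variance of the arm difference is proportional to (1 − ICC) + m·ICC. If only the first term shrinks, the ratio is [(1 − ICC)(1 − r²) + m·ICC] / [(1 − ICC) + m·ICC].

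- ICC 0.01, r = 0.5: (0.99 × 0.75 + 0.116) / (0.99 + 0.116) = 0.858/1.106 = 0.78. For r = 0.3 and 0.7 the ratios are 1.017/1.106 = 0.92 and 0.621/1.106 = 0.56.
- ICC 0.10, r = 0.5: (0.90 × 0.75 + 1.158) / (0.90 + 1.158) = 1.833/2.058 = 0.89. For r = 0.3 and 0.7 the ratios are 1.977/2.058 = 0.96 and 1.617/2.058 = 0.79.

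The factors in Step 1 are therefore the favourable end.

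**Step 3: how large a chance imbalance is likely.** Design effect DE = 1 + (m − 1)·ICC. The SD of the standardised imbalance in prior cost is √[DE × (1/(10m) + 1/(9m))], where 1/115.8 + 1/104.2 = 0.01823.

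| ICC | DE | SD of imbalance | Chance that it exceeds 0.2 SD in either direction |
|---|---|---|---|
| 0.01 | 1.106 | 0.142 | 16% |
| 0.05 | 1.529 | 0.167 | 23% |
| 0.10 | 2.058 | 0.194 | 30% |

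Individual randomisation of 220 gives √(2/110) = 0.135 and a chance of 14%.

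**Step 4: what such an imbalance does.** Unadjusted, an imbalance of 0.2 SD shifts the cost difference by 0.2 × r = 0.06, 0.10 or 0.14 SD. At ICC 0.01 the standard error of the unadjusted cost difference is 0.142 SD, so the shift is 0.06/0.142 = 0.42, 0.10/0.142 = 0.70 or 0.14/0.142 = 0.99 standard errors.

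**The case against.** The strongest reply is that an unadjusted cost comparison in a randomised trial is valid, that a window covering the costed follow-up is coherent, and that the choice of cost covariates belongs in an analysis plan that is not shown. Validity on average is conceded. The choice of covariates may be left to that plan, but the extraction window is stated here and limits what it can choose.

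A reader might infer several stronger things that the document does not support:

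- **That no cost can be adjusted for its history.** Registered sick leave enters the indirect cost, and its 24-month history is extracted. The gap is confined to direct health care cost.
- **That nothing could reveal or reduce an imbalance.** Baseline anxiety, depression, exhaustion, work ability, quality of life and insomnia, prior sick leave, and stratification by care-need index give partial, indirect protection. Eligibility also narrows the range of prior cost: it excludes severe mental disorders, psychiatric referral, pregnancy and somatic disorders affecting work ability, and limits age to 18–59.
- **That the cost result would be biased.** Chance imbalance is already part of the standard error: at ICC 0.01 the 95% half-width is 1.96 × 0.142 = 0.28 SD, against a shift of 0.10 SD at r = 0.5. Recruitment after randomisation does not change this on the document's account, since the screener is blinded to allocation and both arms receive the same information.
- **That having only 19 clusters makes the problem severe.** At the article's ICC the chance of an imbalance above 0.2 SD is 16%, against 14% under individual randomisation. A larger role for clustering requires an assumed higher ICC for cost.

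It also stands that the size of the gain rests on an assumed correlation.

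**Conclusion.** The point holds as a cheap improvement to the economic evaluation. As the windows are written, direct health care cost cannot be adjusted for a participant's own prior health care cost, and the available covariates are only proxies. This weighs most in the cost-effectiveness analysis, where direct cost plus intervention cost is the entire cost side. It weighs less in the cost-utility analysis, where direct cost is one part of societal cost.

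The loss is one of precision and conditional balance. At assumed correlations of 0.3 to 0.7, the interval for the direct-cost difference could be 5% to 29% narrower with adjustment (factors 0.95 to 0.71). The gain is smaller to the extent that between-coordinator variance is left unexplained, or if the proxies already carry part of the information. The precision argument does not depend on the number of clusters.

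**What to change.** Extend the Vega extraction to 24 months before baseline, matching the sick leave extraction, and state this in both the Economic evaluation and the Prognostic measures sections. Compute pre-baseline health care cost per participant with the same unit costs as follow-up. Pre-specify it as a covariate in the direct-cost models of both economic analyses, included whether or not the arms look unbalanced, and report it by arm at baseline. Vega covers only the region, so add a rule for participants who moved in during those 24 months.

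The cost is a longer date range in a register request that is being made anyway and possibly an ethics or data-access amendment. No further contact with participants is needed.

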### Evaluation of ethical issues

An ethical analysis will be performed focusing on central ethical values and norms for the Swedish health care system: patient autonomy and privacy, equality and fairness as well as professional ethos and integrity. The ethical analysis will analyse whether the changes brought about through the intervention will emphasise or mitigate ethical challenges in relation to this patient group. Data will be collected through focus groups interviews with the different stakeholders: employees, employers, rehabilitation coordinators, physicians responsible for sickness certification, social insurance agency officers and representatives of occupational health services. Interview guides based on an ethics framework used in health-technology assessment will be developed [48]. Focus group interviews will be analysed using manifest content analysis.

Based on the results from the focus groups interview and taking into considerations the actual changes implied by the intervention, strategies for how to handle identified ethical challenges or problems will be developed. The methodology of reflective equilibrium will be used, where strategies are developed to be consistent with established ethical values and norms within the Swedish health care system, as found in the Swedish health care legislation and in health care practice [49–51].

#### Randomization

The study has a two-armed cluster randomized design and takes place at the level of RCs. The RCs are randomized into the intervention group or the control group (CAU) by means of computer-generated random numbers. The randomization is stratified according to the PCCs care-need index. This index includes variables such as age, education, employment status, single household and single parent for all persons belonging to each PCC. The index is expected to have an impact on the results and consequently a balance within the strata is required.

A RC covers between one and three PCCs. The RCs in the Västra Götaland region have their own networks and meetings four times a year. Because it is important to avoid contamination, the RCs allocated to the intervention arm are instructed to talk about the intervention only with each other.

#### Blinding

This study has a cluster-randomization design, in which the employees follow the RCs at the PCCs and are randomized before they give informed consent. The employees in both the intervention and the control group receive the same information about the study to equalize employees’ expectations about their participation in the study. The employees are blinded for the treatment allocation since they receive no information about the other group. The RCs are instructed not to tell employees that the study consists of two groups, to ensure that the employees are not aware about the two conditions. The RCs are not blinded for treatment allocation because the RCs in the intervention arm will know that they will receive education and training. An independent statistician will perform the analyses and will be blinded for participant allocation.

#### Data analysis

Statistical analyses adapted for cluster-randomized controlled trials will be conducted. Linear and generalized linear models will be used. Intention-to-treat analyses and, if relevant, per-protocol analyses will be conducted. Potential confounders will be adjusted for in the analyses, if they prove to be unevenly distributed and might be expected to have an impact on the outcomes when the intervention is compared with the control condition. Possible interaction effects on the primary and secondary outcomes for (1) gender x treatment, and (2) number of sessions with RC x treatment will be assessed. If they are statistically significant, appropriate analyses will be considered. Data collected from interviews and focus groups will be analyzed by methods adapted for qualitative data and normative analysis (cf. [48, 52, 53]).

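### Adjustment triggered by observed imbalance would normally leave the stratification factor out of the primary model and use prior sick leave only by chance

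*Protocol article*

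**What the plan says.** The only adjustment rule in the protocol article is in Data analysis: "Potential confounders will be adjusted for in the analyses, if they prove to be unevenly distributed". The same sentence attaches a second condition, that the variable is thought likely to influence the results of the comparison. No covariate is named for the primary model, and no threshold for uneven distribution is given. The model family is stated only as "Linear and generalized linear models will be used", within analyses suited to cluster randomization.

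Two variables stand out as candidates for that model:

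- **Care-need index.** Randomization states: "The randomization is stratified according to the PCCs care-need index". It gives the reason: "The index is expected to have an impact on the results and consequently a balance within the strata is required".
- **Prior sick leave.** Registered sick leave states: "Data from MiDAS will be collected from baseline until the 18-month follow-up and for the 24 months before baseline". Prognostic measures lists it among the variables expected to predict sick leave: "sick leave two years before inclusion will be collected from the LISA and MiDAS registers". It is the pre-baseline counterpart of the primary outcome, which is defined as follows: "The primary outcome is the total number of days of sick leave 18 months after baseline".

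**The concern.** The rule selects covariates by whether the arms differ. Under randomization, what a covariate contributes depends mainly on how strongly it predicts the outcome. Three consequences follow.

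1. A factor that the design balances will usually fail the imbalance condition. The variable that the authors call prognostic and build into the randomization is therefore the one least likely to be modelled. If it does predict sick leave, the variation between strata stays in the error term although the design has removed it from the arm comparison.
2. The 24-month sick-leave history, already collected from the register, is used only in the minority of trials in which it differs enough to be noticed.
3. The covariate set of the primary analysis is fixed only after the arms have been compared, with no stated criterion.

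At stake is precision. Statistical power plans for 10 clusters per arm and around 80% power, and Recruitment of rehabilitation coordinators reports 19 coordinators in all.

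**Working it through.** **Planned power.** Inputs from Statistical power: 10 clusters of 11 per arm, intra-cluster correlation 0.010, alpha 0.05 (taken as two-sided).

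- Design effect = 1 + (11 − 1) × 0.010 = 1.10. Effective size = 110 / 1.10 = 100 per arm.
- Difference detectable with 80% power = (1.960 + 0.842) × √(2/100) = 0.396 SD.

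The document gives no SD, mean or control rate, so its 80% cannot be reproduced from its own inputs. It is consistent with a 20% difference equal to about 0.396 SD. Effects in SD units below are therefore assumptions.

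**Omitting prior sick leave.** Assumed: true effect 0.4 SD, correlation r between prior and follow-up sick leave, 100 independent participants per arm, no strata. Adjustment multiplies the residual variance by 1 − r².

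- r = 0.3: variance down 9%, worth 1/0.91 − 1 = 10% more participants.
- r = 0.5: variance down 25%, worth 1/0.75 − 1 = 33% more participants.

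A conditional rule rarely captures this gain. The SE of a standardized baseline difference is √(2/100) = 0.141. A trigger at p < 0.05 therefore fires in 5% of trials, one at 0.2 SD in about 16% (0.2/0.141 = 1.41), and one at 0.1 SD in about 48% (0.1/0.141 = 0.71). The document names no trigger, so all three are assumptions.

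Simulated power (thousands of trials per cell, repeat runs within about one point):

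| Analysis | r = 0.3 | r = 0.5 |
|---|---|---|
| Unadjusted | 81% | 80% |
| Adjust if baseline p < 0.05 | 81% | 82% |
| Adjust if difference > 0.2 SD | 82% | 83% |
| Adjust if difference > 0.1 SD | 83% | 86% |
| Always adjust | 84% | 91% |

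The closed form for always adjusting agrees: power = Φ(0.4/√(1 − r²) × √50 − 1.96), which is 84% at r = 0.3 and 90% at r = 0.5. Type I error under the conditional rules was between about 4% and 5%.

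**Omitting the stratum.** Assumed: two equal strata with means at ±a SD, 5 clusters per arm in each, analysis of cluster means with 18 df, effect 0.396 SD.

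- True variance of a cluster mean within a stratum = 0.01 + 0.99/11 = 0.10.
- Without a stratum term, the pooled within-arm estimate has expectation 0.10 + 10a²/9.
- a = 0.1: 0.111, so the SE is too large by √(0.111/0.10) = 1.05.
- a = 0.2: 0.144, so the SE is too large by √(0.144/0.10) = 1.20.

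Simulation (8,000 trials per setting) shows the consequence:

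| Stratum means | Type I error, no stratum term | Power, no stratum term | Power, stratum term |
|---|---|---|---|
| ±0.1 SD | about 4% | about 73% | about 76% |
| ±0.2 SD | about 2% | about 62% | about 75–77% |

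With no stratum effect, leaving the term out costs nothing. These figures start nearer 76% than 80% because 18 df are used in place of the normal approximation.

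**The case against.** Several points on the other side stand.

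- **The index is not barred.** A reader might infer that the rule excludes the care-need index outright. It does not. Stratification is at coordinator level, a coordinator covers one to three centres, and there are 19 coordinators, so participants may still be unbalanced on the index and it could qualify. The supportable wording is that it would normally be left out.
- **Not every omission makes the standard error wrong.** A reader might infer that leaving out prior sick leave also makes the standard error too large for the analysis done. Only the stratum has that effect, because only the stratum was used to restrict the randomization. Without prior leave the analysis is valid but less precise.
- **No false-positive problem was shown.** A reader might infer from data-dependent covariates that type I error is inflated. It is not in these calculations. The trigger looks at covariates rather than outcomes, and the Blinding section has the analysis done by a statistician blinded to allocation.
- **The planned power does not rely on covariates.** In the prior-leave calculation the rule does not fall below about 80%; the loss is of extra power that was available.
- **Imbalance here may not be chance alone.** Coordinators are randomized before employees consent, so differential recruitment is possible and looking at balance has a legitimate purpose. This supports keeping such adjustment as a sensitivity analysis.

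It can also be said that a condensed article may leave the covariate list to an analysis plan. That would answer a complaint about silence. It does not answer this one, because the article states a rule, and that rule sits badly with its own reason for stratifying.

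**Conclusion.** The point holds. The stated rule would normally leave out a stratification factor that the protocol expects to be prognostic, which makes inference conservative if that expectation is right. It would use the 24-month sick-leave history only when the arms happen to differ, and it settles the covariate set after the arms are compared.

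The size cannot be taken from the documents. For prior leave, the gap between always adjusting and a conditional rule runs from about 1 point (r = 0.3, sensitive trigger) to about 9 points (r = 0.5, p < 0.05 trigger). For the stratum it runs from nothing to about 14 points at stratum means of ±0.2 SD. The effect in SD units, the correlations, the trigger, the number of strata and the stratum effects are all assumptions. The existence of the defect depends on none of them. It is a matter of lost precision and avoidable discretion, and it should be corrected.

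**What to change.** In Data analysis, replace the conditional rule with a fixed one:

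- The primary model includes care-need-index stratum and registered sick-leave days in the 24 months before baseline, whatever the observed balance. Age and gender, already listed under Prognostic measures, may be added.
- Each questionnaire outcome is also adjusted for its own baseline value.
- Cluster-level terms are kept few, and a small-sample correction suited to about 19 clusters is used.
- The unadjusted result, and a model adding any other covariates found to be imbalanced, are reported as sensitivity analyses only. The second is worth keeping because employees are recruited after coordinators are randomized.

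The cost is a change of wording, best made before the arms are compared. The stratum is known from the randomization, and the other variables are already to be collected.
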